The objective of this study is to investigate the effects of the liftless intervention on the incidence of PTB and LBW among pregnant Ghanaian women. This study aims (1) to provide guideline-oriented and social support (liftless intervention) to Ghanaian women to reduce their lifting behavior during pregnancy; (2) to evaluate the effect of the liftless intervention on rates of PTB, LBW, mode of delivery, lower back or pelvic pain, and premature uterine contractions compared to no such intervention; and (3) to examine compliance with the intervention and ascertain factors that influence it.

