### Outcomes

#### Primary outcome

The primary outcome is gestational age based on ultrasound examination in the first trimester (before 16 weeks), or when not available, fundal height and last menstrual period. We expect that only about 10% of the pregnancies will be without ultrasound diagnosis. We will still include these to prevent increasing the workload of the recruiting midwives. We will conduct a sensitivity analysis to see if there is an effect of the ultrasound versus last menstrual period and fundal height diagnosis. We will categorize PTB as extremely preterm (<28 weeks), very preterm (28-32 weeks), or moderate to late preterm (33-37 weeks) based on the World Health Organization classification [30].

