#### Secondary outcomes

The secondary outcomes are as follows:

Birthweight categorized as preterm LBW, full term but LBW, or postterm LBW babies [7].Compliance with the intervention (classified as compliant or noncompliant). We will classify a participant as compliant (1) if the weight and frequency of lifting have decreased to below the provisional guidelines and (2) if lifting below or above the knee or shoulders has decreased, based on the participant’s self-reported lifting and observations during home and workplace visits.Prevalence of lower back pain or pelvic pain: yes or no; frequency: sometimes or most of the time; stage of pregnancy: first or second or third trimester; severity: mild or moderate (interferes with daily function or severe and needs analgesics to subside).Premature uterine contractions: yes or no; frequency: sometimes or most of the time; stage of pregnancy: first or second or third trimester.Mode of delivery: normal or forceps or cesarean section, as recorded on birth and postnatal records.

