**Figure 2 figure2:**
[figure not shown]
Flow of the trial (adopted from Standard Protocol Item: Recommendations for International Trials 2013).

Inclusion criteria.Inclusion criteria1. Pregnancy has been clinically confirmed.2. Pregnancy is between 12 and 16 weeks.3. Pregnancy is singleton.4. Exposed to lifting of 10 kg at home or work.5. Attending 1 of 10 antenatal clinics.6. Participant has consented to participate in the trial.

Exclusion criteria.Exclusion criteria1. Pregnancy has not been confirmed.2. Gestational age is above 16 weeks.3. Multiple pregnancies.4. Not exposed to lifting.5. Not attending any of the selected clinics.6. Refusal to participate.

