### Data Collection Tools and Data Management

First, a 55-item questionnaire will be used to collect sociodemographic data, baseline information on gestational age, family support, history of work activities, exposure to heavy lifting or carrying, lifting below the knee or above the shoulders, frequent bending, daily hours of standing, and repetitive movement. Second, the lifting and carrying diary will be used to assess participants’ self-reported daily frequency and weight of lifting and carrying and compliance. Third, participants’ antenatal and postnatal cards will be used to assess gestational age, birthweight, mode of delivery, and history of premature uterine contractions. The cards are usually filled out by midwives who provide antenatal care and deliver the child. Finally, the intervention session booklet will be used to record session attendance, participants’ complaints, and summary of education given. Any text data generated during home visits and telephone calls to or from the participants will also be recorded.

Data and materials obtained during the trial will be transferred and stored electronically, with a back-up on two memory sticks under the supervision of the primary researcher. The digital data will be disposed after dissemination and publication of the results.

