### Statistical Analysis and Sample Size

We will compare the average proportion of all outcomes in the intervention group clusters to the control group clusters. We will test our hypothesis using a logistic regression model with a random effect for cluster and a fixed effect for each step of implementation of the intervention to adjust for possible effects of calendar time [34,35].

If there are major baseline differences between the intervention and control clusters for potential confounders, such as prolonged standing or squatting, parity, maternal age, infection, occupation, educational level, marital status, and nutritional status, we will include these as covariates in the model. Intention to treat will be the basis for the statistical analysis to ensure that all clusters (with participants) are randomized and included in the final analysis regardless of completion of the study or not [36].

For the sample size calculation, we set alpha at 0.1 and beta at 0.8. We assumed that the intervention will decrease PTB rate by 30% (ie, from 14.5% to 10.5%, with 14.5% being the current official PTB rate in Ghana). With 10 antenatal clinics, we estimated that we need 1000 participants to provide the power to detect a 30% difference in the rate of PTB between the control and intervention clusters. The individual performing the analysis will be blinded to the treatment allocation.

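### Back or pelvic pain and premature contractions may be scored from the first trimester, most of which precedes enrolment, and no outcome window starts at enrolment

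*Protocol article*

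**What the plan says.** All references are to the protocol article.

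- **Secondary outcomes.** Pain is recorded as "lower back pain or pelvic pain: yes or no; frequency: sometimes or most of the time; stage of pregnancy: first or second" or third trimester, with a severity grade. Contractions are recorded in the same form: "Premature uterine contractions: yes or no; frequency: sometimes or most of the time; stage of pregnancy: first or second or third trimester".
- **Inclusion criteria (textbox).** "Pregnancy is between 12 and 16 weeks".
- **Primary outcome.** Pregnancies are dated by "ultrasound examination in the first trimester (before 16 weeks", so the article takes the first trimester to run up to week 16.
- **Study Design.** The intervention is given in five extra weekly sessions, once the woman's clinic is in its intervention phase.
- **Data Collection Tools and Data Management.** The antenatal and postnatal cards supply "gestational age, birthweight, mode of delivery, and history of premature uterine contractions". The topics listed for the 55-item baseline questionnaire include neither pain nor contractions.
- **Introduction, aim 2.** The trial is to evaluate the effect on "lower back or pelvic pain, and premature uterine contractions compared to no such intervention".
- **Statistical Analysis and Sample Size.** "We will compare the average proportion of all outcomes in the intervention group clusters to the control group clusters". No period at risk is given for either symptom outcome, and neither symptom is among the example covariates.

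**The concern.** An outcome used to estimate an intervention effect should be able to respond to the intervention. Here the outcome definitions name a stage of pregnancy that lies largely before a woman can be in the trial. If a woman with back pain at 8 weeks is scored positive, she stays positive whichever phase her clinic is in and whatever she lifts afterwards.

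Such events should occur about equally in both conditions, so they would not create a false benefit. They would shrink a real difference and cost power, and a null result for pain or contractions would be hard to interpret. Symptoms already present at entry are also useful prognostic information, which is lost if they are merged into the outcome.

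**Working it through.** **Plan's own figure.** The article gives no rate, effect or power for pain or contractions. Its only design figure, 1000 participants, concerns preterm birth. With one-sided alpha 0.10, power 0.80 and 14.5% against 0.7 × 14.5% = 10.15%, the two-proportion formula without clustering gives 514 per group, 1028 in total, close to 1000. The point below does not depend on it.

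**Step 1: timing.** Let *e* be the week of enrolment, from 12 to 16. Taking the first trimester to end at week 16, the part after enrolment is 16 − *e* weeks.

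- *e* = 12: 4 of 16 weeks (25%) follow enrolment.
- *e* = 14: 2 of 16 weeks (12.5%).
- *e* = 16: none.

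Weeks 0 to 12 precede enrolment for everyone. At least 12/16 = 75% of the category, counted in weeks, does so for each woman.

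**Step 2: what is counted.** Set side by side, the definitions admit the first trimester, the cards supply contractions as a history without a start date, and the analysis compares the proportions of all outcomes. No sentence removes pre-enrolment events.

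**Step 3: effect on the contrast.** Assumptions, none from the article: a fraction *f* of women has early symptoms, equal in both conditions and independent of later symptoms; risk after enrolment is *c* under control and *t* under intervention.

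Observed proportions are *f* + (1 − *f*)*c* and *f* + (1 − *f*)*t*. Their difference is (1 − *f*)(*c* − *t*), so it always shrinks by the factor 1 − *f*.

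With *c* = 40% and *t* = 30% (25% relative reduction):

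| *f* | Control | Intervention | Difference | Relative reduction |
|---|---|---|---|---|
| 0 | 40% | 30% | 10 points | 25% |
| 20% | 52% | 44% | 8 points | 8/52 = 15.4% |
| 30% | 58% | 51% | 7 points | 7/58 = 12.1% |
| 40% | 64% | 58% | 6 points | 6/64 = 9.4% |

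**Step 4: effect on power.** Further assumptions: 500 per group, two-sided alpha 0.10, no clustering or stepped-wedge structure, true risk ratio 0.70. With *p̄* the mean of the two proportions,

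power = Φ{[ |p₁ − p₂|√n − 1.645√(2p̄(1 − p̄)) ] / √(p₁(1 − p₁) + p₂(1 − p₂))}.

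| *c* | *f* | Control v intervention | Risk ratio | Power |
|---|---|---|---|---|
| 20% | 0 | 20.0% v 14.0% | 0.700 | 0.812 |
| 20% | 10% | 28.0% v 22.6% | 0.807 | 0.625 |
| 20% | 20% | 36.0% v 31.2% | 0.867 | 0.485 |
| 20% | 40% | 52.0% v 48.4% | 0.931 | 0.306 |
| 40% | 0 | 40.0% v 28.0% | 0.700 | 0.991 |
| 40% | 10% | 46.0% v 35.2% | 0.765 | 0.967 |
| 40% | 20% | 52.0% v 42.4% | 0.815 | 0.920 |
| 40% | 40% | 64.0% v 56.8% | 0.888 | 0.753 |

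The absolute power values are not predictions for this trial. The table shows how the loss grows with *f*, and that it is steeper when later symptoms are less common.

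**The case against.** **The counting rule is not spelled out.** The article lists what is recorded and does not say which stages enter the comparison. A reader might infer that the plan expressly counts any first-trimester symptom as an outcome event; it does not say so. Because stage is recorded, early events could be set aside in the analysis, and a fuller document might do that. This limits the point but does not remove it: the outcome definition itself names a largely pre-enrolment stage, and nothing shown takes it out again.

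**Not every first-trimester event precedes enrolment.** A reader might infer that all of them do. The article's own limit of 16 weeks overlaps the entry window by up to about four weeks, and a woman entering at 12 weeks in an intervention-phase clinic could attend several sessions in that time. This stands. It also means that restricting the outcome to the second and third trimesters would discard some symptoms that arise after entry.

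**Baseline symptoms may be collected.** The 55-item questionnaire is only summarised, and the covariates are given as examples. The documents do not support saying that baseline pain or contractions are not recorded.

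**A start at enrolment is not a complete remedy.** Symptoms that arise after entry but before a woman's clinic crosses over also precede the intervention. This is true, but it is a separate matter of how such women are assigned to a condition.

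**The consequence is limited.** The expected bias is toward no difference, and two of five secondary outcomes are involved. This also stands.

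**Conclusion.** The point holds in a limited form. As written, both definitions admit symptoms from a stage that lies wholly or largely before enrolment, no text limits a positive score to the period after enrolment, and the analysis treats the resulting proportions as intervention effects. Events before week 12 cannot be affected in any participant.

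The direction, dilution toward no difference, rests on early symptoms being about equally frequent in the two conditions. The size is unknown. The illustrated risk ratios of 0.77 to 0.93 in place of 0.70 rest entirely on assumed rates, on independence of early and later symptoms, and on counting every early symptom as an event. The primary outcome and the sample size are untouched. The definition is worth correcting because the change is nearly free and the Results section says that funding is still being sought.

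**What to change.** 1. Define both outcomes as symptoms occurring after the date of enrolment. Set the boundary by that date and not by trimester. Symptoms that began earlier but continue after enrolment still count, so the outcome remains a prevalence.
2. Keep the stage-of-pregnancy field as descriptive information.
3. Record pain and contractions up to enrolment at the baseline interview, adding an item to the 55-item questionnaire if it has none.
4. State that this baseline status will be a covariate in the logistic model for the corresponding outcome, whether or not the groups differ at baseline.
5. When contractions are taken from the cards, note whether they occurred before or after enrolment.

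The cost is a few sentences of protocol wording, at most one baseline item and slightly more care in reading the cards. No visits or participants are added. Reported prevalence will be somewhat lower than an any-time-in-pregnancy figure, and the report should say so.

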**Figure 1 figure1:**
[figure not shown]
Stepped-wedge design. Shaded boxes: intervention phases; white boxes: control phases. (Adopted from a trial protocol by Hill AM, Waldron N, Etherton-Beer C, et al 2014).

**Figure 2 figure2:**
[figure not shown]
Flow of the trial (adopted from Standard Protocol Item: Recommendations for International Trials 2013).

Inclusion criteria.Inclusion criteria1. Pregnancy has been clinically confirmed.2. Pregnancy is between 12 and 16 weeks.3. Pregnancy is singleton.4. Exposed to lifting of 10 kg at home or work.5. Attending 1 of 10 antenatal clinics.6. Participant has consented to participate in the trial.

Exclusion criteria.Exclusion criteria1. Pregnancy has not been confirmed.2. Gestational age is above 16 weeks.3. Multiple pregnancies.4. Not exposed to lifting.5. Not attending any of the selected clinics.6. Refusal to participate.

### Randomization and Blinding

Using a computer-generated number sequence, the 10 antenatal clinics will be randomized as to when the intervention is implemented. To ensure internal validity of the study, the randomization will be carried out by a professional who is not involved in the delivery of the treatment or its assessment [31]. This will be done before the trial begins. However, due to the nature of the project, neither the research midwives nor participants can be blinded to the treatment allocation. However, a data analyst who will perform the final analysis will be blinded to the treatment allocation.

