## Methods

### Study Design

We propose an open cohort stepped-wedge cluster RCT (PACTR201602001301205). In this design, eligible participants will be recruited until the expected numbers have been achieved. The design is a unidirectional cross-over study wherein all participating antenatal clinics will start with a control phase and eventually end up providing the intervention. The intervention will not be withdrawn once implementation has begun (at least not until the end of the trial). Participants will leave the trial when they deliver. Baseline measurements and information will be collected in all 10 clusters at the beginning of the trial using a 55-item data collection tool. Using random allocation, two clusters will transition into the intervention with each phase lasting 10 weeks. With the exception of clusters 1 and 2 (Figure 1) [27], the rest of the clusters will contribute data to the control more than once. Clusters 9 and 10 will contribute control data at 5 time points before the intervention is implemented. Thus, unlike a traditional cluster RCT where the intervention is administered only to those in the treatment group, every cluster in the stepped-wedge RCT will receive the intervention. The flow of the trial is shown in Figure 2 [28].

During the control phases, participants will receive routine antenatal care including physical and abdominal examination, blood pressure and weight measurement, urine testing, prescription of iron and folic acid supplementation, and tetanus injection. When a clinic enters the intervention phase, in addition to receiving routine antenatal care, participants will attend 5 extra intervention sessions at weekly intervals. During the sessions, study midwives will deliver the 3-component liftless intervention explaining and demonstrating all of the potential harmful task conditions, providing a take-home reminder card, and soliciting for a partner’s support. In addition, midwives will make phone calls, do home visits, and provide the shopping vouchers.

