### Study Population and Recruitment

The trial will be conducted at 10 public antenatal clinics in Ghana (the lists of clinics are provided in Multimedia Appendix 1). Eligible clinics will be those that offer antenatal services. The selected clinics are located in 4 cities in Ghana. The clinics will recruit 1000 participants within a period of 60 weeks. Although the facilities vary in size, they are located in areas that have sufficient numbers of pregnant women to make the trial feasible. The socially ascribed activities of most women within the catchment areas of the proposed antenatal clinics include carrying water and farm produce on their heads as well as carrying market wares as street vendors. Most women also carry their younger children on their backs at home, to the market, and to the farm. Additional antenatal clinics will be added to meet the planned target if necessary. The study midwives will recruit participants based on the prespecified participant-level criteria (Textboxes 1 and 2). The nature of the trial and the required commitment on the part of participants will be explained to the participants by the research midwives in a language that they understand. Participation is voluntary and decisions will not affect the routine antenatal care they will receive. Those who agree to participate and are eligible will be provided with a consent form to sign or thumb print (the copy of consent form is available on request from the authors).

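### Unblinded midwives recruit in both phases after clinic order is set, and the conditional covariate rule is a weak guard against a case-mix shift at crossover

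*Protocol article*

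**What the plan says.** All references are to the Protocol article.

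- **Allocation.** Under Randomization and Blinding, a person outside delivery and assessment randomises the order in which the 10 clinics switch: "This will be done before the trial begins". The same section says that "neither the research midwives nor participants can be blinded to the treatment allocation". The final analyst is blinded.
- **Recruitment.** Study Design describes an open cohort in which "eligible participants will be recruited until the expected numbers have been achieved". Study Population and Recruitment adds: "The clinics will recruit 1000 participants within a period of 60 weeks", and "The study midwives will recruit participants based on the prespecified participant-level criteria". The midwives also explain the trial and its commitment before consent.
- **Delivery.** Under Study Design, "study midwives will deliver the 3-component liftless intervention". Recruiter and deliverer are the same role.
- **Eligibility.** The inclusion criteria textbox asks for "Exposed to lifting of 10 kg at home or work". It gives no frequency, no reference period and no means of checking.
- **What women receive.** In control phases they get routine antenatal care. In intervention phases "participants will attend 5 extra intervention sessions at weekly intervals", with telephone calls, home visits and six vouchers of 40 GH₵ during pregnancy (Component 3). The Discussion says that control participants get vouchers after birth.
- **Analysis.** Statistical Analysis and Sample Size specifies a logistic model with a random cluster effect and fixed step effects. Covariates are added only if baseline imbalance between intervention and control clusters is judged large. The examples include parity, maternal age and education, but not baseline lifting.

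**The concern.** Randomising clinics balances what is fixed about a clinic. It does not protect who enters the trial afterwards, when the person deciding on eligibility and seeking consent knows the current phase. Two routes are open. A midwife may read a loosely worded lifting criterion more generously in one phase than in the other. A woman may accept or decline because the sessions, calls, visits and voucher timing differ. If risk of preterm birth differs between the women enrolled before and after a clinic's switch, that difference enters the primary comparison. It could produce an apparent benefit or conceal a real one, and the blinded analyst cannot undo it.

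**Working it through.** **1. Must women be recruited after allocation, under both conditions?** Women enter at 12-16 weeks and leave at delivery. Taking delivery at about 40 weeks (an assumption), each is followed for 40 − 16 = 24 to 40 − 12 = 28 weeks. Clusters 9 and 10 give control data at 5 time points with 10-week phases, so they switch at about 5 × 10 = 50 weeks. A woman enrolled at the start has delivered long before that. Recruitment therefore has to continue after allocation and across each clinic's switch.

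**2. Does the planned model remove a shift at crossover?** Written out, the model is

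logit P(PTB) = μ + clinic effect + step effect + θ·X,

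where X is 0 before and 1 after the clinic's switch. Suppose selection changes log-odds by δ among women enrolled after the switch. The linear predictor becomes μ + clinic effect + step effect + (θ + δ)·X. The clinic effect absorbs stable differences between clinics, and the step effect absorbs calendar trends that all clinics share. Neither follows X, so the model estimates θ + δ.

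**3. Does the covariate rule catch it?** Only in part. It depends on what is seen in the data, and the article gives no threshold. It is framed as a comparison of clusters, although every clinic supplies both conditions and the shift in question lies within a clinic, between phases. Its examples omit baseline lifting, the variable most exposed to a generous or strict reading of the entry criterion, although the 55-item questionnaire collects it.

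**4. How large could it be?** The documents give no figure, so this is illustration. With no true effect,

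false difference = p × s × (1 − r),

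where p = 14.5% (Statistical Analysis and Sample Size), s is the share of intervention-phase recruits who would not have joined in a control phase (assumed), and r is their risk relative to the others (assumed). The planned effect is 14.5 − 10.5 = 4.0 points.

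| s | r | false difference | share of 4.0 points |
|---|---|---|---|
| 0.1 | 0.7 | 0.145 × 0.1 × 0.3 = 0.44 points | 11% |
| 0.2 | 0.7 | 0.145 × 0.2 × 0.3 = 0.87 points | 22% |
| 0.2 | 0.5 | 0.145 × 0.2 × 0.5 = 1.45 points | 36% |
| 0.3 | 0.5 | 0.145 × 0.3 × 0.5 = 2.18 points | 54% |

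The sign follows r. With s = 0.2 and r = 1.3 the result is 0.145 × 0.2 × (1 − 1.3) = −0.87 points, which would hide a benefit. Other assumptions move the range: s from 0.1 to 0.5 with r from 1/1.3 to 1/2 gives 0.3 to 3.6 points.

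**5. Women still pregnant at the switch.** Follow-up of 24-28 weeks spans more than two 10-week steps, so many women enrolled under control conditions will be pregnant when their clinic crosses over. If they count as intervention and form a fraction g of that group, the false difference shrinks by the factor (1 − g). The documents do not give g.

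**The case against.** Several points against a stronger reading stand.

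- A reader might infer that entry rests on self-reported lifting. The article uses that term for compliance and the diary, not for eligibility. All it shows is that no check is stated and that a questionnaire is the only entry-stage source named.
- A reader might infer that control women are offered nothing beyond routine care. Vouchers after birth are planned for them, so that contrast is one of timing. The sessions, calls and home visits still differ.
- A reader might infer that consent information differs by phase. The consent form is not shown. Because many control-phase women will cross over while pregnant, their consent may well already cover the whole trial.
- Crossover during pregnancy blurs the two groups, so enrolment phase and exposure do not coincide.
- The shares and relative risks in the illustration have no source in the documents. A relative risk of 0.5 is stronger than the trial's own target of 10.5/14.5 = 0.72.
- Lack of blinding during delivery is unavoidable and openly stated, and is not itself the fault.

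These points limit how much can be claimed. They leave the core in place: unblinded recruiters share the deliverers' role, they enrol across the switch, and the stated adjustment is conditional and does not name baseline lifting.

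**Conclusion.** The point holds as a risk that the design leaves open, with a weak analytic guard against it. The documents show that case mix can shift with phase. They do not show that it will, in which direction, or by how much. The 0.4-2.2 point range is conditional on assumed shares of 10-30% and assumed relative risks of 0.5-0.7, and should not be read as an estimate. Two parts of the plan can be improved: the data-dependent covariate rule and the order of steps at enrolment. The article reports that funding was still being sought, so both could be changed before recruitment starts.

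**What to change.** 1. **Statistical Analysis and Sample Size.** Replace the conditional covariate rule with adjustment in every case for a short fixed list: baseline lifting exposure, parity, maternal age and education. Lifting exposure is on the baseline questionnaire, and the other three are already named as potential confounders.
2. **Study Population and Recruitment.** Have midwives approach consecutive women at 12-16 weeks. Complete eligibility, consent to the whole trial and the 55-item baseline form before the woman is told her clinic's current phase. If the consent form already describes the whole trial, say so in this section.

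The cost is a little more analysis work and a stricter enrolment order. Residual bias remains because the midwives still know the phase, and adjustment cannot reach factors that are not measured.
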